3	Individual provider interviews	12 MCM providers (1 administrator and 1 direct-service provider per partnering agency)	Providers’ experience of the pilot, barriers and facilitators, or other factors for pilot tool implementation, and any recommendations	September 2023 to February 2024	Qualitatively assess pilot implementation factors and outcomes and desired changes to piloted tools
3	Program data on patients enrolled and pilot-related service delivery	≥180 MCM patients from 6 partnering agencies	Patient descriptive data, assessments of patient ART regimen and adherence, and detail on pilot services delivered (tools and dates used, as well as patient responses on ART regimen choices)	May 2023 to January 2024, with follow-up on LAI ART adherence through September 2024	Quantitatively assess pilot implementation outcomes such as reach, effectiveness, adoption, and implementation and variation by agency, intervention condition, or stage of pilot

^a^MCM: medical case management.

^b^LAI: long-acting injectable.

^c^ART: antiretroviral therapy.

The study functions as an academic-government-provider collaboration, with a university-based lead agency working closely with a health department and 6 NY RWPA MCM service-provider agencies that were engaged as partners from the outset. The 6 provider agencies were purposively selected to represent the full range of NY RWPA MCM service settings (hospitals, community health centers, and social services community-based organizations) and the distinct geographic regions within the NY RWPA eligible metropolitan area. Three of the agencies have headquarters in NYC, which includes 5 counties: New York (Manhattan), Bronx, Kings (Brooklyn), Queens, and Richmond (Staten Island). The other 3 agencies have headquarters in the Tri-County area north of NYC: Westchester, Rockland, and Putnam. All 6 agencies had an annual caseload of at least 70 RWPA MCM patients at the time of the study proposal development. Although the FDA had not approved LAI ART until after the study proposal was submitted, LAI ART prescription was beginning when the project started and was being considered for some MCM enrollees at the partner agencies by the second year of the project in the months immediately preceding the pilot.

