#### Study Outcomes

##### LAI Uptake (Primary Outcome)

The primary outcome is defined as the proportion of pilot participants who start LAI ART (whether initiating ART, transitioning from a prior regimen, or transitioning from a period of nonuse of ART). The denominator includes patients not already on LAI ART at the start of the pilot trial, and the numerator includes any of those in the denominator who began LAI ART during the trial. Using program-reported (eSHARE) data on regimen type, uptake will be measured continuously for up to 9 months (the duration of the pilot trial). *Concordance:* This outcome is defined as the proportion of participants whose intent (as documented via the decision aid) is carried through in terms of their subsequent treatment (self-administered daily oral ART, LAI ART, or some intermediate step such as directly observed therapy to meet the current FDA label requirement for viral suppression). Using eSHARE data on decision aid responses and subsequent regimen type or services related to ART adherence, concordance will be measured from the date of decision aid completion for up to 9 months. *LAI maintenance:* LAI maintenance is defined in terms of adherence to LAI ART, specifically the time from LAI initiation to first deviation from the injection schedule, among trial participants initiating LAI ART during the trial. A deviation includes any injection >1 week ahead of or 1 week after the treatment target date, where the injection target date depends on whether the prescribed regimen is monthly or bimonthly. Using eSHARE data on ART regimen type and adherence (as well as case closure owing to death), maintenance will be measured from the first report of LAI ART to the first reported deviation from the injection schedule or date of death from any cause, whichever comes first, assessed for up to 9 months from the first injection or up to 8 months of follow-up injections (counting from the first possible deviation from a scheduled follow-up injection).

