##### Sample Size, Data Analysis, and Power Analysis

The original target was to enroll 180 patients or 30 (on average) per partner agency. As of mid-November 2023, 205 patients were enrolled. Using eSHARE data, we will describe trial participant demographics (eg, gender, age, race or ethnicity, income, and housing status) overall and by intervention arm. We will compare LAI ART uptake and, among those starting LAI ART, adherence by intervention arm, to assess the effects of the fuller package with the decision aid versus education alone. We will use log binomial regression to estimate risk ratios for uptake and adherence by intervention arm with generalized estimating equations and a small sample correction (owing to the small number of clusters) to maintain the type I error rate while accounting for clustering by site. To the extent possible given our sample size, we will adjust for potential confounders captured in eSHARE.

The brief provider survey measures will be analyzed through a comparison of responses on the same measures over time (eg, to assess change in perceived feasibility), as well as comparison of responses by intervention arm, agency type, and participant role. AIM, IAM, FIM, and ORIC scores will also be analyzed in relation to the levels of pilot service delivery as documented in eSHARE. To understand the potential for sustainability and scale-up, we will explore qualitative provider interview themes related to the acceptability and feasibility of the intervention. Qualitative and quantitative analyses will be integrated by examining thematic patterns reflecting RE-AIM and CFIR implementation constructs as they explain observed implementation outcomes [61].

Our pilot was designed to assess implementation of the newly developed tools and inform tool refinements. Data from the pilot will be used to generate estimates of LAI ART uptake that can, in turn, inform sample size and power calculations for a larger, controlled study of the refined tools’ implementation and treatment outcomes. Accordingly, data from the pilot study will be used to estimate the proportion of patients who start LAI ART and, among those initiating, the proportion who maintain LAI ART. With the original target of 180 patients (now exceeded), we will be able to estimate LAI uptake with precision (95% CI) with the levels of uptake described in Table 2.

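### LAI uptake, the primary outcome, is tied to the trial calendar rather than to each patient's enrolment, so patients with unequal time at risk are analysed as a simple proportion

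*Protocol article*

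**What the plan says.** Under LAI Uptake (Primary Outcome), the protocol article states: "The primary outcome is defined as the proportion of pilot participants who start LAI ART". The base is fixed at trial opening: "The denominator includes patients not already on LAI ART at the start of the pilot trial". Starts are then counted until trial close: "the numerator includes any of those in the denominator who began LAI ART during the trial". On timing, "uptake will be measured continuously for up to 9 months (the duration of the pilot trial"). The two outcomes defined next to it have a patient-level origin: concordance runs from completion of the decision aid, and maintenance from the first injection.

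Table 1 gives the period for the program data as "May 2023 to January 2024, with follow-up on LAI ART adherence through September 2024", so the extension covers adherence and not uptake. Enrolment was staggered: "As of mid-November 2023, 205 patients were enrolled" (Sample Size, Data Analysis, and Power Analysis). The same section gives the analysis: "We will use log binomial regression to estimate risk ratios for uptake and adherence by intervention arm". Clustering by site is handled by GEE, corrected for the few clusters. It adds that the uptake estimate will inform the sample size of a larger controlled study. Under Nonrandom Assignment, three agencies were purposively placed in each arm, with attention to agency type and program size.

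**The concern.** An ever/never proportion can be interpreted when everyone is observed for the same time after the event of interest, here receipt of the tools. In this plan the numerator closes when the trial closes, so a patient reached late has less time to start LAI ART than one reached early, and both count as complete observations. Starting also takes time by the article's own account: insurance preauthorization is named as a barrier (Aim 1 Focus Groups), and an intermediate step such as directly observed therapy may precede LAI ART (LAI Uptake).

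Two results are at stake. The uptake percentage passed to the next trial would mix follow-up times and correspond to no fixed interval after tool receipt. And a difference in enrolment timing between the two groups of agencies could appear as an effect of the decision aid, since the assignment does nothing to balance that timing.

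**Working it through.** **The plan's own figures.** Wilson score intervals with n = 180 ("The original target was to enroll 180 patients or 30 (on average) per partner agency") reproduce Table 2 within 0.1 percentage point. At 20% uptake, for example, they give 14.8-26.4. Maintenance at 50% reproduces with n = 180 × uptake. Each patient is therefore treated as one complete binomial observation.

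**Follow-up after enrolment.** Take the trial as 9 months, from the start of May 2023 to the end of January 2024 (the exact start day is assumed). Mid-November is month 6.5, so a patient enrolled then has 9 − 6.5 = 2.5 months. If accrual was uniform to that point, follow-up is uniform on 2.5-9 months, with mean (2.5 + 9)/2 = 5.75.

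**Observed uptake, true 9-month uptake 20%.** The article gives neither start times nor accrual by agency, so two shapes are assumed.

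- *Constant rate:* F(t) = 1 − exp(−λt), with λ = −ln(0.80)/9 = 0.0248 per month. The mean of F over follow-up a to b is 1 − [exp(−λa) − exp(−λb)]/[λ(b − a)]. For a = 2.5 and b = 9 this is 1 − (0.9399 − 0.8000)/0.1612 = 0.132.
- *Front-loaded:* F(t) = 0.20 × (1 − exp(−t/m))/(1 − exp(−9/m)), that is, exponential start times among starters with scale m months, scaled to reach 20% at 9 months. Averaged over 2.5-9 months, m = 2 gives 0.185 and m = 4 gives 0.164.

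**Risk ratio with no true arm effect.** This is the ratio of mean F in the earlier-enrolling arm to that in the later-enrolling arm.

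| Follow-up, earlier v later arm (months) | Constant rate | Front-loaded, m = 4 | Front-loaded, m = 2 |
|---|---|---|---|
| Same in both | 1.00 | 1.00 | 1.00 |
| 5-9 v 3-7 | 0.159/0.116 = 1.37 | 1.17 | 1.07 |
| 6-9 v 2.5-6 | 0.169/0.100 = 1.70 | 1.31 | 1.13 |

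If the decision-aid arm is the one that enrols later, the inverses apply (for example 1/1.70 = 0.59).

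**Sensitivity to lead time.** If no one can start in the first 2 months and the rate is constant afterwards, observed uptake falls to 11.1% and the two ratios rise to 1.62 and 2.34. This is an unfavourable assumption and is not used in the conclusion.

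**Against the planned precision.** At 20%, Table 2's lower limit is 20 − 14.8 = 5.2 points below the estimate. The shortfall is 20 − 13.2 = 6.8 points under a constant rate, and 3.6 or 1.5 points under the front-loaded shapes.

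**The case against.** The strongest reply is that the wording defines one calendar window for all: not on LAI ART when the trial began, started before it ended. Patients were already in case management with regimen type reported in eSHARE (Data Collection and Management), so this can be measured, and the period is defined. That answers a claim that no period is stated. It does not rescue the outcome as a measure of the tools: starts before tool receipt would count as uptake, and time after receipt would still vary.

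A reader might also infer that some patients were followed for only days. The article does not support this, because no enrolment closing date is given and January enrolment is not documented. Uniform accrual to the last day would lower an observed 20% to 10.4%. It would also imply about 205/6.5 × 2.5 = 79 further patients, which no section reports.

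A constant start rate may be severe too. The decision aid records an agreed plan at a visit, so early starts are plausible, and the front-loaded rows show how far that shrinks the problem.

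Finally, adjustment for confounders captured in eSHARE is promised where the sample allows, and tool dates are recorded there, so an analysis plan could adjust for timing. That could reduce the arm bias. It could not recover starts after January 2024, which the stated numerator excludes, or give the proportion a common horizon.

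**Conclusion.** The concern holds as a fault in the time origin and window of the primary outcome. Time at risk after tool receipt varies, from about 2.5 months for a mid-November enrolee to 9 months for the earliest, and the stated analysis ignores this. Uptake is understated relative to a common 9-month horizon: a true 20% would appear as about 13% under a constant start rate and about 16-18% under front-loaded starts, given uniform accrual to mid-November.

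The arm bias is conditional. It is absent with identical accrual, and null risk ratios run from about 1.1 to 1.7 under the two accrual differences shown. Whether the arms did enrol at different times is not reported. It would go too far to say that the estimate reflects enrolment pace rather than the tools. The article also presents the pilot as a source of preliminary effects and planning estimates, but an uptake figure used for planning needs a defined interval.

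**What to change.** Set eligibility (not on LAI ART) and time zero at each patient's pilot enrolment or first tool receipt. Define uptake as a start within a fixed window, for example 8 months, and extend eSHARE uptake capture to September 2024. Even a patient enrolled at the end of January 2024 would then have 8 months. Alternatively, keep the January 2024 cut-off and estimate cumulative incidence with administrative censoring. In either case, censor at closure of the case-management record, apply the same fixed window to concordance, and report enrolment timing by agency and arm.

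The data cost is small: eSHARE is extracted monthly, adherence is already followed to September 2024, and complete outcome data are not expected until October 2024. There are two real costs. Starts after the pilot closes would be counted, when other LAI initiatives or label indications may have changed. And a change of outcome measure must go through investigator agreement, advisory board vetting and an IRB modification, as set out under Ethical Considerations.

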##### Other Measures

To understand the influences on implementation, we assess provider-perceived acceptability, appropriateness, and feasibility of the tools at 3 points in the pilot: baseline, 4-5 months (midpoint), and 9 months (end of the pilot). Specifically, the provider survey includes the 4-item scales (AIM, IAM, and FIM) that were used in the provider DCE survey [52]. However, for the pilot survey, these 3 measures specifically refer to the pilot tools being implemented. The baseline and midpoint assessments also include a brief measure of organizational readiness for implementing change (ORIC), which captures commitment to change (5 items) and perceived efficacy to change (7 items) [59] based on the theory of organizational readiness for change [60]. As the ORIC measure is anticipatory, it is not part of the final assessment. The semistructured midpoint and end-of-pilot interviews elicit providers’ experiences of the piloted tools, including barriers, facilitators, and suggested refinements. Interviews will lend context to the ORIC, AIM, IAM, and FIM results and guide tool refinements.

##### Sample Size, Data Analysis, and Power Analysis

The original target was to enroll 180 patients or 30 (on average) per partner agency. As of mid-November 2023, 205 patients were enrolled. Using eSHARE data, we will describe trial participant demographics (eg, gender, age, race or ethnicity, income, and housing status) overall and by intervention arm. We will compare LAI ART uptake and, among those starting LAI ART, adherence by intervention arm, to assess the effects of the fuller package with the decision aid versus education alone. We will use log binomial regression to estimate risk ratios for uptake and adherence by intervention arm with generalized estimating equations and a small sample correction (owing to the small number of clusters) to maintain the type I error rate while accounting for clustering by site. To the extent possible given our sample size, we will adjust for potential confounders captured in eSHARE.

The brief provider survey measures will be analyzed through a comparison of responses on the same measures over time (eg, to assess change in perceived feasibility), as well as comparison of responses by intervention arm, agency type, and participant role. AIM, IAM, FIM, and ORIC scores will also be analyzed in relation to the levels of pilot service delivery as documented in eSHARE. To understand the potential for sustainability and scale-up, we will explore qualitative provider interview themes related to the acceptability and feasibility of the intervention. Qualitative and quantitative analyses will be integrated by examining thematic patterns reflecting RE-AIM and CFIR implementation constructs as they explain observed implementation outcomes [61].

Our pilot was designed to assess implementation of the newly developed tools and inform tool refinements. Data from the pilot will be used to generate estimates of LAI ART uptake that can, in turn, inform sample size and power calculations for a larger, controlled study of the refined tools’ implementation and treatment outcomes. Accordingly, data from the pilot study will be used to estimate the proportion of patients who start LAI ART and, among those initiating, the proportion who maintain LAI ART. With the original target of 180 patients (now exceeded), we will be able to estimate LAI uptake with precision (95% CI) with the levels of uptake described in Table 2.

Assuming that half of the people who initiate LAI ART maintain it at 9 months, we will have the abovementioned precision estimates for the scenario of 50% LAI ART maintenance across a range of different levels of LAI ART uptake.

**Table 2 table2:** 95% CIs for long-acting injectable (LAI) antiretroviral therapy (ART) uptake among pilot participants overall and maintenance estimates for those who start on LAI ART under LAI uptake percent assumptions.

LAI ART uptake, (%)	LAI ART uptake, 95% CI	LAI ART maintenance at 50%, 95% CI
5	2.7-9.2	22.7-77.4
10	6.4-15.2	29.0-71.0
15	10.5-20.9	32.4-67.7
20	14.8-26.4	34.5-65.5
30	23.8-37.0	37.0-62.9
40	33.1-47.3	38.8-61.3
50	42.8-57.3	39.9-60.1

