#### Study Setting and Participants

The pilot test was conducted at the 6 partnering RWPA MCM agencies. The characteristics and study arm assignments of the 6 agencies are summarized in Multimedia Appendix 1. Cluster (agency-level) assignment was used for this study to minimize crossover between intervention conditions and avert the logistical and ethical dilemmas posed by assignment strategies that require providers to administer, maintain, and track different investigator-assigned intervention conditions within a single patient caseload [54-56]. *Provider eligibility:* Pilot-related primary data collection was limited to English-speaking adults responsible for overseeing or delivering RWPA MCM services or prescribing ART for MCM patients at a partnering agency. At each agency, 1 administrative staff member (eg, program director) and 1 direct-service provider (eg, case manager, patient navigator, or prescriber) was engaged to participate in implementation-related data collection through brief surveys and semistructured interviews. *Patient eligibility:* Patients were enrolled in a partnering NY RWPA MCM program, aged ≥18 years, and able to understand materials in English or Spanish. Patient eligibility for an LAI ART prescription could not be directly assessed by the study team and could be assessed differently by different providers or third-party payers; it could also change over time with FDA label indications. However, the study team communicated to partnering programs that patients should not be included in the pilot if they had known or suspected resistance to cabotegravir or rilpivirine, as this was a contraindication for LAI ART available as of the start of this pilot study (CABENUVA). On the basis of AB feedback that translating pilot materials to Spanish without translating to Haitian Creole would be viewed as inequitable, and given a lack of remaining time or resources to provide translations for tools (including audio for the video) in 3 languages, the pilot study was launched with only English-language tool versions.

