##### Nonrandom Assignment

We used purposive sampling to assign 3 of the 6 partnering RWPA MCM agencies to the decision-aid arm (which included the educational tools) and 3 to the education-only arm. Specifically, we ensured representation of at least 2 different agency types and MCM program sizes in each arm.

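### Table 2's 95% CIs for LAI ART uptake treat 180 patients from 6 agencies as independent, so the stated precision is too narrow for any positive intracluster correlation

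*Protocol article*

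**What the plan says.** The design is clustered. Under Study Setting and Participants: "Cluster (agency-level) assignment was used for this study to minimize crossover between intervention conditions". Under Nonrandom Assignment, the team used purposive sampling to "assign 3 of the 6 partnering RWPA MCM agencies to the decision-aid arm", and the other 3 went to the education-only arm. The sample size section adds: "The original target was to enroll 180 patients or 30 (on average) per partner agency".

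For the arm comparison, that section plans a log binomial model fitted by GEE, and it specifies this adjustment: "small sample correction (owing to the small number of clusters) to maintain the type I error rate while accounting for clustering by site".

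The precision statement comes two paragraphs later: "With the original target of 180 patients (now exceeded), we will be able to estimate LAI uptake with precision (95% CI". Table 2, which it refers to, is titled as giving "95% CIs for long-acting injectable (LAI) antiretroviral therapy (ART) uptake among pilot participants overall", followed by maintenance among those who start. The maintenance column assumes that 50% of initiators maintain LAI ART. Neither the text nor the table mentions an ICC, a design effect, an effective sample size or an assumption of independence.

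**The concern.** The section treats patients within an agency as correlated for one purpose and appears to treat them as independent for another. The 6 agencies were chosen to span hospitals, community health centers and community-based organizations, in New York City and in the Tri-County area, so some variation in uptake between agencies is to be expected. Six clusters of about 30 patients then carry less information on overall uptake than 180 unrelated patients.

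What is at stake is the one quantitative statement the article makes about what its sample size achieves. The article says that the pilot's uptake estimates will feed sample size and power calculations for a larger controlled study, so readers should not be given a better impression of their precision than the design supports.

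**Working it through.** **Inputs from the protocol article.** N = 180; 6 agencies, so m = 30 per agency on average; uptake levels of 5% to 50%; maintenance 50% among initiators; 205 patients enrolled by mid-November 2023. **Assumed, because no ICC is given:** ICC from 0.01 to 0.10, and equal agency sizes.

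**Step 1. Reproduce Table 2.** The Wilson interval for a proportion p on n independent patients is

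[p + z²/2n ± z√(p(1−p)/n + z²/4n²)] / (1 + z²/n), with z = 1.96.

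For maintenance, p = 0.5 and n = 180 × uptake.

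| Uptake | Computed, n=180 | Printed | Initiators | Computed maintenance | Printed |
|---|---|---|---|---|---|
| 5% | 2.65-9.23 | 2.7-9.2 | 9 | 22.65-77.35 | 22.7-77.4 |
| 10% | 6.42-15.25 | 6.4-15.2 | 18 | 29.03-70.97 | 29.0-71.0 |
| 15% | 10.52-20.94 | 10.5-20.9 | 27 | 32.35-67.65 | 32.4-67.7 |
| 20% | 14.81-26.44 | 14.8-26.4 | 36 | 34.47-65.53 | 34.5-65.5 |
| 30% | 23.78-37.06 | 23.8-37.0 | 54 | 37.11-62.89 | 37.0-62.9 |
| 40% | 33.12-47.29 | 33.1-47.3 | 72 | 38.75-61.25 | 38.8-61.3 |
| 50% | 42.77-57.23 | 42.8-57.3 | 90 | 39.88-60.12 | 39.9-60.1 |

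Taken to one decimal, every limit agrees within 0.1 point; a few differ in the last digit. Wald, Clopper-Pearson, Jeffreys and Agresti-Coull intervals do not fit all rows this closely. The table therefore contains no clustering allowance.

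**Step 2. Uptake with clustering.** The design effect is DE = 1 + (m−1) × ICC = 1 + 29 × ICC, and the effective n is 180/DE. For example, at ICC 0.05, DE = 1 + 29 × 0.05 = 2.45 and 180/2.45 = 73. The 20% row, printed as 14.8-26.4, becomes:

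| ICC | DE | Effective n | Wilson at effective n | Same, t on 5 df | Simulated coverage of the unadjusted interval |
|---|---|---|---|---|---|
| 0.01 | 1.29 | 140 | 14.2-27.4 | 12.7-30.0 | about 92% |
| 0.02 | 1.58 | 114 | 13.7-28.3 | 12.1-31.2 | about 88% |
| 0.05 | 2.45 | 73 | 12.5-30.5 | 10.7-34.2 | about 79% |
| 0.10 | 3.90 | 46 | 11.0-33.6 | 9.1-38.4 | about 68% |

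Coverage is from beta-binomial simulation with 6 clusters of 30 and true uptake 20%. The half-width grows roughly by √DE: about 1.14 times at ICC 0.01, 1.57 at 0.05 and 1.97 at 0.10. Other rows behave alike: at ICC 0.05, 10% uptake gives 5.0-19.0 (printed 6.4-15.2) and 50% gives 38.9-61.1 (printed 42.8-57.3).

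**Step 3. Maintenance with clustering.** Here m is the number of initiators divided by 6. At ICC 0.05:

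| Initiators | m | DE | Adjusted | Printed |
|---|---|---|---|---|
| 9 | 1.5 | 1.03 | 22.4-77.6 | 22.7-77.4 |
| 18 | 3 | 1.10 | 28.2-71.8 | 29.0-71.0 |
| 36 | 6 | 1.25 | 32.8-67.2 | 34.5-65.5 |
| 90 | 15 | 1.70 | 37.0-63.0 | 39.9-60.1 |

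The design effect barely matters for 9 or 18 initiators and is visible at high uptake. A t reference on 5 df widens even the first row, to 17.2-82.8, because there are only 6 clusters.

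**Step 4. Does enrolling 205 repair it?** With m = 205/6 = 34.2 and ICC 0.05, DE = 1 + 33.2 × 0.05 = 2.66, effective n = 205/2.66 = 77, and the 20% row is 12.6-30.3. At ICC 0.01 it is 14.5-27.0, still wider than printed. The extra patients offset clustering only if DE is at most 205/180 = 1.139, which means an ICC of at most 0.139/33.2, about 0.004.

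**The case against.** The strongest reply is that this is a pilot for assessing and refining tools. It makes no power claim, its enrolment target does not rest on Table 2, and that target has been passed. The inferential analysis already allows for clustering with a small-sample correction, and the Results section commits to the CONSORT extension for cluster trials. Table 2 is an illustration at hypothetical uptake levels that observed data will replace. All of this stands and limits the severity. It does not make the printed intervals right.

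A second reply is that the size of the shortfall depends on an ICC that nobody has stated, and that at 0.01 the change is modest. That is correct. Only the direction is independent of the ICC's value, given that it is positive.

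A third is that the 6 agencies were purposively chosen partners. If the target were uptake in exactly these agencies, treated as fixed strata, variation between them would not be sampling error and the table could be defended. The article does not say this, and using the estimates to plan a larger study points beyond the 6 agencies. The reply is still a reason to treat the 5-df figures as indicative.

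Two further criticisms are tempting, and the documents do not support them:

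- **Pooling the arms.** A reader might call this an error, but the table's title says that it describes participants overall, and the text sets out to estimate that overall proportion.
- **The denominator.** A reader might object that 180 is too large, because "The denominator includes patients not already on LAI ART at the start of the pilot trial". The article gives no count of pilot patients already on LAI ART. The nearest figure is 9/201 (4.5%) who had ever tried it in the separate patient preference survey. If a similar share left the 205, about 196 would remain (205 × 0.955), more than the 180 used.

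**Conclusion.** The point holds for the stated precision of uptake. Table 2 describes a simple random sample of 180, which is not the design in the article. For any positive ICC its uptake intervals are too narrow for 180 patients in 6 agencies. At 20% uptake the width is 11.6 points as printed (26.4 − 14.8), against 13.2 at ICC 0.01 (27.4 − 14.2) and 22.6 at ICC 0.10 (33.6 − 11.0), before any allowance for having only 6 clusters. For maintenance the design effect is negligible at 5-10% uptake and moderate at the top of the table.

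These sizes rest on the assumed ICC range and equal agency sizes; unequal caseloads would raise the design effect. A reader might infer that the pilot is too small, that its arm comparison is invalid, or that the next trial will be mis-sized. The documents support none of these: no sample size or test depends on Table 2, the arm comparison accounts for site, and nothing says that the observed overall estimates will be reported without adjustment. Severity is moderate to minor.

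**What to change.** Restate Table 2 over a range of ICCs, for example 0.01, 0.02, 0.05 and 0.10, using effective n = n/(1 + (m−1) × ICC). Take m = 30 for uptake and m = initiators/6 for maintenance; a single cluster size of 30 would overcorrect the maintenance rows. Use a reference distribution matched to the number of clusters, and state the assumed ICCs next to the table.

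In the results, report overall uptake and maintenance with cluster-adjusted intervals, and give the observed ICC so that the larger study can use it.

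The cost is a recalculated table, a sentence of explanation and less favourable stated precision. No more patients are needed, and the planned arm comparison does not change.
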